#### Exercise prescription

Generally, an effective exercise program is conducted 3 times per week for 3 months (12 weeks) [30]. In considering the participants who are a group of older adults without regular exercise experience may need more time to adapt to regular exercise, a longer duration by extending the intervention period to 4 months (16 weeks) will be adopted in this study. With 3 sessions per week, the duration of each session will be 60 min, which include 10 min of warm-up, 40 min of main exercise, and 10 min of cool-down. The intensity will be light to somewhat hard (RPE 11 to 13; using the Cantonese version of RPE) [31]. In resistance training, the weights (resistance) will be from participants’ own bodies, dumbbells, and adjustable ankle weights.

The simple equipment and forms of training selected in the current study is for sustainability of training after the intervention. The participants could continue their training at homes or at the senior centers as no sophisticated equipment required for the training. The dumbbell weights used in the resistance training program are 1 kg, 2 kg, 3 kg, and 4 kg for women and 2 kg, 3 kg, 4 kg, 5 kg for men, and the adjustable ankle weights are from 1 kg to 10 kg, based on the reference of the book “*Growing Stronger: Strength Training for Older Adults”* [32] as well as advice of PFA. The intensity of each exercise will be 3–4 sets with 10–12 repetitions per set. Adjustment will be made in accordance with individual’s level of fitness as well as adaptability and progression of the training. The improvement will be on progressive and safe manner under proper guidance of the coach. Each participant will be provided a log-book for recording the intensity, progression, and personal feedback of training for evaluation during and after the training.

In Tai Chi, the 16-week program will be divided into cognitive, associated, and automatic stages. The coach will apply a group teaching with individual instruction on specific movements based on participant’s needs in skills learning and acquisition. The same training principles of individuality and progression as well as training log-book used in resistance training will also be applied to Tai Chi training program. In order to achieve a safe and effective teaching and learning, both resistance training and Tai Chi groups will be randomly divided into two sub-groups, with 20 participants in a sub-group. It means that 2 sub-groups of resistance training as well as 2 sub-groups of Tai Chi training, which will be conducted in separate timeslots but taught by the same coach of the program (one coach for resistance training, and one coach for Tai Chi training) at the same venue so as to ensure both sub-groups will receive similar teaching and learning quality.

#### Intervention group (resistance training)

Participants will receive a 16-week resistance training program, with 3 times a week (a total of 48 training sessions) and 60 min per session intervention, which is adopted from the 12-week resistance training program introduced in the book “*Growing Stronger: Strength Training for Older Adults”* (Seguin et al., 2002), with minor modifications under the advice of PFA. Below is the sketch of the resistance training program which will be taught by the qualified resistance training coach recommended by PFA (see Table 1).

**Table 1 Tab1:** Training program for the strength training group

Strength Training	Warm-up (10′)	Exercises (40′): 3–4 sets with 10–12 repetitions per set	Cool-down (10′)
**Part I (week 1–2)** To strengthen body slowly and gently using only own body weight	light walking and stretching	Six exercises: squats, wall push-ups, toe stands, finger marching, pelvic tilt, floor back extension	light walking and stretching
**Part II (week 3–6)** To strengthen body slowly and gently, using own body weight and light dumbbells	light walking and stretching	Eight exercises: squats, wall push-ups, toe stands, finger marching, pelvic tilt, floor back extension, biceps curl, overhead press	light walking and stretching
**Part III (week 7–10)** To increase exercise to 10, and add adjustable ankle weights	light walking and stretching	Ten exercises: squats, wall push-ups, toe stands, finger marching, pelvic tilt, floor back extension, biceps curl, overhead press, knee extension, knee curl	light walking and stretching
**Part IV (week 11–16)** To increase exercise to 12, with less resting time between sets	light walking and stretching	Twelve Exercises: squats, wall push-ups, toe stands, finger marching, pelvic tilt, floor back extension, biceps curl, overhead press, knee extension, knee curl, step-ups, side hip raise	light walking and stretching

#### Active concurrent control group (tai chi)

The active concurrent control group will receive Eight-form Yang-style Tai Chi program which has been confirmed feasible and will be taught by the qualified coach recommended by HKWU (see Table 2).

**Table 2 Tab2:** Training program for the Tai Chi group

Tai Chi	Warm-up (10′)	Exercises (40′)	Cool-down (10′)
**Part I (week 1–4)** Cognitive stage	light walking and stretching	**Learn the following movements with the coach guidance**: Repulse Monkey, Brush Knee Twist Step, Part Wild Horse’s Mane, Wave Hands in Clouds, Golden Rooster Stand on one Leg, Heel Kick, Grasp Swallow’s Tail, and Cross Hand	light walking and stretching
**Part II (week 5–10)** Associated stage	light walking and stretching	**Refine all the movements with supervision.**	light walking and stretching
**Part III (week 11–16)** Automatic stage	light walking and stretching	**Play all the movement by oneself smoothly.**	light walking and stretching

#### Non-treatment concurrent control

Participants in this group will not participate in any specific intervention during the whole study (the 16-week intervention and 12-week follow-up periods), but they will be asked to keep a daily log on their physical activity, medicine used, illness, diet, sleep quality and other health and physical activity related information (e.g., attending healthy eating workshops). In addition, participants of the control group will be asked to report to the research assistant (RA) if a major change has been made in the aforementioned aspects. The RA will also check the daily logs of the participants through telephone every 2 weeks. Data from those who had changed their normal lifestyles (especially taking up regular physical activity) will be examined for exclusion in the subsequent data analysis.

### Outcome measures

#### Primary outcome – resilience

In order to meet the needs of the local older population, the Chinese version of RS (CRS) [33] will be used to measure participants’ resilience in the study. The CRS was modified from the Resilience Scale developed by Wagnild and Young [34] with subsequent validation in Chinese older population and confirmed its four-factor structure: equanimity, meaningfulness, ceaseless self-improvement, and self-reliance. A 7-point Likert scale from 1 (highly disagree) to 7 (highly agree) is used, with a greater score mirroring higher level of resilience. Three levels are set, with scores of 145 and above indicating moderate to high resilience, scores from 126 to 144 indicating low to moderate levels of resilience, and scores less than 126 indicating low resilience. The internal consistency (Cronbach’s α) for the total scale was 0.95, and the test–retest reliability was 0.80 [33].

#### Secondary outcomes: functional fitness

The functional fitness (FF) of participants will be measured using the Senior Fitness Test (SFT) battery [35]. The SFT is a widely used measurement for functional fitness of older adults [36] in the ageing and physical activity area. It was first developed and validated by Rikli and Jones [37] with the purpose of early identification of older individuals at risk for losing functionality. There are 7 testing items assessing all the 5 dimensions of functional fitness, including body mass index (BMI), 30s chair stand for lower limbs’ muscle strength, 30s arm curl for upper limbs’ muscle strength, 2 min step test for aerobic endurance, chair sit-and-reach test for lower body flexibility, back scratch test for upper body flexibility, and 8 ft. up-and-go test for mobility and dynamic balance [37]. Rationales behind the SFT along with the validity and reliability of these testing items have been well described in Senior Fitness Test Manual [35]. The present study will strictly follow the testing procedures as suggested by this manual. The testing team supported by PFA will be invited to conduct the test. The testing team was trained to complete the SFT for about 1000 older adults in our previous study for establishing FF norms for Hong Kong older adults [38]. All the tests will be conducted before (pre-test) and after (post-test) the 16-week interventions. In order to examine how long the training effect might persist, a follow-up test will be carried out at beginning of the13^th^ week, 12 weeks after completion of the intervention (follow-up test).

#### Secondary outcomes: health related quality of life

The Short Form-36 (SF-36) is a widely used health survey questionnaire, especially for older adults to assess the health related quality of life (HRQoL) [39]. The SF-36 consists of 36 items covering two dimensions—physical health (physical functioning, role limitations due to physical problems, role limitations due to emotional problems, and social functioning) and mental health (mental health, vitality, body pain, and general health perception). In the current study, the Chinese version of the SF-36 (C-SF-36) will be used. The C-SF-36 was translated and validated by Li and colleagues [40], which has demonstrated satisfactory test–retest reliability (r = 0.66–0.94). In our previous study using the C-SF-36 as the measure for the older adults [41], we found that the Cronbach alpha was 0.846 for the physical dimension and 0.837 for the mental dimension of quality of life, indicating that the Chinese version of the SF-36 has high convergent validity.

### Data analysis

Descriptive statistics will be used to describe baseline characteristics such as age, body weight, gender, resting heart rate, living status (alone or with family) of the participants in the study. The primary outcomes (resilience scores) will be analysed using an intention-to-treat (ITT) approach, and a sensitivity test will subsequently be conducted using the available data. Missing data will be replaced using the last observation carried forward method. For the secondary outcomes, per-protocol analysis will be conducted using the available data. The statistical significance level was set at *p* < .05. All data will be analyzed using SPSS Version 24.0 (IBM, Chicago, IL).

For the within group test, a one-way repeated measure analysis of variance (ANOVA) will be applied to each group to determine the changes of each outcome parameter among the three time points (i.e., pre-test, post-test, and follow-up test). When the sphericity assumption was violated, the Greenhouse–Geisser correction will be used when epsilon < 0.75, or the Huynh–Feldt correction will be used when epsilon > 0.75 [42]. Post hoc analysis with Bonferroni correction will be conducted to explore the differences between the pre-test and post-test, as well as post-test and follow-up test. The mean differences with 95% confidence intervals (CIs) will be reported. For the inter-group test, a one-way analysis of covariance (ANCOVA) with the baseline value as a covariate will be conducted at the post-test, and follow-up test to determine the group effect on each outcome parameter. Subsequently, the differences between the resistance training group and control groups as well as between the resistance training and Tai Chi groups will be analysed through planned contrasts. The effect size r was calculated manually according to r = sqrt [t2/(t2 + df)]. According to Cohen [43], r = .10, .30, and .50 represent a small, medium, and large effect size, respectively. The whole project is expected to complete within 18 months.

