## Methods

### Study design

This study will apply a three-group, double blinded (outcome assessors and data analysts), randomised controlled trial (RCT) to examine the effectiveness of the interventions on resilience, functional fitness, and health related quality of life immediately after a 16-week intervention, as well as the residual effects 12 weeks after completion of the interventions. The double blinding adopted in this study is to reduce the bias and to ensure that those who are collecting the outcome measures (such as research assistants collecting data via questionnaires and fitness assessors collecting data from the functional fitness test), and those who are inputting and analysing the data, have no knowledge regarding groups allocation status of the study participants [21].

In assigning the groups, the CONSORT procedure will be followed [22]. The three groups will be resistance training group, Tai Chi group, and control group. Tai Chi will be selected as an active concurrent control group for adding value in the comparison. The reason for choosing Tai Chi is because it has been proven to help the heart-failure patients improve their self-efficacy and self-esteem of resilience measured by the Resilience Scale [23]. Also, the aerobic type of Tai Chi will also demonstrate a bigger contrast to the anaerobic type of resistance training and therefore, the comparison on the training effects between resistance training and Tai Chi will add value to selection of exercise for future training and intervention of further study. Ethical approval from the Research Ethics Committee of the Hong Kong Baptist University has been obtained.

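### Fitness and quality-of-life outcomes are analysed per-protocol only, so no comparison of all participants as randomised is planned for them

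*Protocol article*

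**What the plan says.** Under Study design, the trial is set up "to examine the effectiveness of the interventions on resilience, functional fitness, and health related quality of life", both after the 16-week programme and 12 weeks later. Resilience is the primary outcome; the Senior Fitness Test items and the SF-36 are labelled secondary.

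Data analysis then gives the two classes different analysis sets:

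- Resilience: "The primary outcomes (resilience scores) will be analysed using an intention-to-treat (ITT) approach", followed by a sensitivity analysis on available data.
- Everything else: "For the secondary outcomes, per-protocol analysis will be conducted using the available data". No intention-to-treat analysis and no sensitivity analysis is named for these outcomes.

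The between-group test is a one-way ANCOVA with the baseline value as covariate. It "will be conducted at the post-test, and follow-up test to determine the group effect on each outcome parameter", and planned contrasts of resistance training with control and with Tai Chi follow.

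The section on the non-treatment control adds a rule for that arm only. Data from control participants who changed their habits ("especially taking up regular physical activity) will be examined for exclusion in the subsequent data analysis") may be left out.

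**The concern.** Randomisation protects a comparison only while people are counted in the arm to which they were allocated. A per-protocol set is chosen on what happened afterwards, and here the opportunity to be excluded differs by arm. Resistance training and Tai Chi each have 3 × 16 = 48 scheduled sessions; the non-treatment arm has none. A rule based on attendance could remove participants from the first two arms but never from the third, whereas the lifestyle-change rule can remove participants only from the third.

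Attendance plausibly goes with health, motivation and fitness, and fitness is the outcome closest to exercise itself. If poor attenders leave the training arms, the remaining trainees would tend to score better than a random sample of those allocated, even if training did nothing. Losing newly active controls would push the same way.

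At stake is whether the trial can say anything about effectiveness for fitness and quality of life. The resilience result and the secondary results would also describe different sets of participants in one report. This is a choice the article states, not a detail it leaves to another document, so an analysis plan that followed it would carry it forward.

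**Working it through.** **1. Analysis sets, side by side**

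| Outcome | In the effectiveness aim? | As-randomised analysis named? | Other analysis named |
|---|---|---|---|
| Resilience | yes | yes (ITT) | available-data sensitivity |
| Functional fitness | yes | no | per-protocol, available data |
| Quality of life | yes | no | per-protocol, available data |

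The carry-forward rule ("Missing data will be replaced using the last observation carried forward method") sits next to the ITT statement. Since the secondary outcomes use available data, it does not supply an as-randomised analysis for them.

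The article states no figure for this point that could be reproduced. The rest is an illustration.

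**2. Inputs**

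- From the article: 40 per arm; 20% anticipated dropout, the only related rate given.
- Assumed: no true effect; a fraction p excluded from one arm, p = 10%, 20% or 30%; correlation r between the tendency to be retained and the outcome of 0.2, 0.4 or 0.6; normally distributed variables.

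**3. Bias before baseline adjustment**

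Excluding the lowest fraction p on a variable correlated r with the outcome shifts the retained mean by

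bias (SD) = r × φ(z_p) / (1 − p),

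where z_p is the p-quantile of the standard normal distribution and φ its density.

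- p = 0.10: 0.1755 / 0.90 = 0.195
- p = 0.20: 0.2800 / 0.80 = 0.350
- p = 0.30: 0.3477 / 0.70 = 0.497

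| Excluded from one arm | r = 0.2 | r = 0.4 | r = 0.6 |
|---|---|---|---|
| 10% | 0.04 SD | 0.08 SD | 0.12 SD |
| 20% | 0.07 SD | 0.14 SD | 0.21 SD |
| 30% | 0.10 SD | 0.20 SD | 0.30 SD |

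With 40(1 − p) trainees against 40 controls, a nominal two-sided 5% test that ignores baseline would reject a true null hypothesis in 5.3% of trials at the mildest corner (10%, r = 0.2), 9.2% in the middle (20%, r = 0.4) and 24.9% at the strongest (30%, r = 0.6).

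**4. After the planned ANCOVA**

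Baseline adjustment removes the part of the selection that baseline carries. Approximately,

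bias = (r − r_xy × r_ax) × φ(z_p) / (1 − p),

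with r_xy the baseline–outcome and r_ax the baseline–attendance correlation, both assumed. At r = 0.4 and 30% excluded (0.20 SD unadjusted):

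| r_xy | r_ax | Arithmetic | Bias |
|---|---|---|---|
| 0.6 | 0.4 | (0.40 − 0.24) × 0.497 | 0.08 SD |
| 0.6 | 0.2 | (0.40 − 0.12) × 0.497 | 0.14 SD |
| 0.7 | 0.4 | (0.40 − 0.28) × 0.497 | 0.06 SD |
| 0.7 | 0.2 | (0.40 − 0.14) × 0.497 | 0.13 SD |

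Simulation of the ANCOVA agrees with these values. The bias vanishes only if r = r_xy × r_ax, that is, if attendance is related to the outcome solely through the baseline score.

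**5. The two planned contrasts**

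- Resistance versus control: attendance selection can act on one side only, so the figures above apply.
- Resistance versus Tai Chi: an attendance rule acts on both sides. With equal fractions and correlations the two shifts cancel. Bias arises only if the programmes differ in who stays.

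**The case against.** Several points against the concern stand and limit it.

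- **Arms are compared.** A reader might infer that fitness and quality of life get no randomised comparison at all. The ANCOVA and the planned contrasts cover every outcome. What is missing is a comparison that keeps everyone as randomised.
- **Per-protocol is undefined.** No attendance threshold is given, and an article may leave that definition to the full protocol. Tied to available data, the term could mean little more than complete cases. That would be milder, but it should then be called that.
- **Control exclusions are discretionary.** It is tempting to say that the worst trainees and the best controls are removed. The text says only that such data will be examined for exclusion, and the monitored aspects include medicine, illness, diet and sleep as well as activity. Removing controls who fell ill would work against training, so the direction is probable, not certain.
- **A larger bias is not supported.** Adding an assumed 20% exclusion of active controls to a 30% exclusion of trainees, both at r = 0.4, gives 0.14 + 0.20 = 0.34 SD, which a reader might set against the 0.30 effect size in the sample-size section. That sum ignores baseline adjustment and rests on assumed inputs. The 0.30 also has no stated metric: if it is the r used in Data analysis, it corresponds to d = 2 × 0.30 / √(1 − 0.09) = 0.63.
- **These are secondary outcomes.** The Background aim is resilience alone, and its planned analysis is ITT. This lowers the stakes, but Study design still names the other two as effectiveness targets.

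None of this supplies an as-randomised analysis for the secondary outcomes.

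**Conclusion.** The point holds in this form: for functional fitness and quality of life, the only analysis named is per-protocol on available data, so effectiveness on these outcomes would be judged in a set selected after randomisation. The resistance-versus-control contrast is the exposed one, and the bias probably favours training; the contrast with Tai Chi is less exposed.

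A plausible size is about 0.04–0.30 SD before baseline adjustment. In the adjusted examples above, 0.20 SD falls to 0.06–0.14 SD. All of these values depend on assumed exclusion fractions and correlations; they show what could happen, not what will. The main resilience conclusion does not depend on this sentence. It should be changed before analysis because the fault lies in a stated choice and is cheap to mend.

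**What to change.** In Data analysis, replace the sentence on secondary outcomes with:

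> Secondary outcomes will be analysed in all randomised participants with outcome data, in their allocated arm and regardless of attendance or lifestyle change, using the same baseline-adjusted ANCOVA and planned contrasts as the primary outcome. A per-protocol analysis, with its criteria defined in advance, will be supplementary only.

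In the section on the non-treatment control, state that exclusions for lifestyle change apply only to that supplementary analysis. That rule is not limited to secondary outcomes as written, so this also keeps it away from the ITT analysis of resilience.

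The cost is two sentences and the same ANCOVA run on a wider set. Outcome assessment has to continue for participants who stop attending; those without outcome data remain missing, and the number per arm should be reported. The downside is that estimates may be smaller than the per-protocol ones.

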### Sample size estimation

Based on the previous intervention studies, the most frequently reported effect size was ranged from moderate (0.30) to high (0.70) [25–29], a moderate effect size at 0.30 will be adopted for the current study. To ensure an 80% probability for detecting a treatment difference at a two-sided 5% level of significance and taking into account a 20% of potential dropout rate [30], a sample size of 40 participants per group (totally 120 for 3 groups) will be required in the current study.

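### Resilience is compared between arms by two contrasts at two visits, all at p < .05, with no test named primary and no adjustment across the four

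*Protocol article*

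**What the plan says.** All of this is in the Data analysis section of the protocol article unless noted.

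- **Level.** "The statistical significance level was set at *p* < .05". It is not divided across contrasts or visits. The Sample size estimation section makes it two-sided: "To ensure an 80% probability for detecting a treatment difference at a two-sided 5% level of significance". It does not say which treatment difference is meant.
- **Visits.** The baseline-adjusted ANCOVA "will be conducted at the post-test, and follow-up test to determine the group effect on each outcome parameter".
- **Contrasts.** After the ANCOVA come two differences: resistance training against control, and between "the resistance training and Tai Chi groups will be analysed through planned contrasts".
- **Correction.** Bonferroni appears once, for the within-group comparisons of pre-test with post-test and of post-test with follow-up. Nothing similar is stated for the between-group contrasts.
- **Ranking.** The Abstract and the Study design section mention the effect straight after the 16-week programme together with residual effects 12 weeks later. Neither section, nor any other, names a primary visit or contrast.

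**The concern.** The randomised between-group comparisons carry the trial's conclusion; the within-group changes do not. Yet the article corrects for multiplicity only in the within-group part.

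Each contrast can also support a claim of its own. The Background and the abstract's Discussion expect resistance training to be promising, or even superior to aerobic training. A significant result against control would support the first part, and one against Tai Chi the second. With two visits and no ranking, any one of four results at p < .05 could be presented as the positive primary finding, and the 5% level would not hold for that finding as a whole.

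**Working it through.** The plan states no family-wise error rate that could be reproduced. Its only figure on this point is 5% per test. The stated sample size is a separate matter and nothing below depends on it.

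**Inputs**

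- Level per test: 0.05, two-sided (Data analysis; Sample size estimation).
- Tests on one resilience score: 2 contrasts × 2 visits = 4.
- Allocation 1:1:1, 40 per arm (Grouping and randomization). With 20% dropout, 40 × 0.8 = 32 per arm.
- Correlation between post-test and follow-up scores after baseline adjustment: **not given, so an assumption**. The main range is 0.4 to 0.8, and 0 to 0.9 is also shown. The nearest figure in the article is the scale's test–retest reliability of 0.80. If all three visits correlated at 0.80, the baseline-adjusted correlation would be (0.80 − 0.80²)/(1 − 0.80²) = 0.16/0.36 = 0.44.

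**Step 1. Upper reference: independent tests**

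- Two tests: 1 − 0.95² = 9.75%.
- Four tests: 1 − 0.95⁴ = 18.5%.

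**Step 2. Allow for the shared arm**

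Both contrasts use the resistance training arm. With equal arms their correlation is (1/n)/(1/n + 1/n) = 0.5. By simulation, two contrasts at one visit then give about 9.0%.

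**Step 3. Four tests over two visits**

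The simulation used 400,000 runs per setting with no difference between arms, t contrasts on the pooled error with 3n − 4 degrees of freedom, and n = 32 and n = 40 per arm. The two sample sizes agree to within about 0.2 percentage points. *Ungated* means the contrasts are always tested. *Gated* means they are tested at a visit only if the overall ANCOVA there has p < .05.

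| Correlation between visits | Ungated, either direction | Ungated, favouring resistance training | Gated, either direction | Gated, favouring resistance training |
|---|---|---|---|---|
| 0 | 17.2–17.3% | 8.8–8.9% | 8.2% | 4.1–4.2% |
| 0.4 | 16.4–16.6% | 8.3% | 7.8–7.9% | 3.9% |
| 0.5 | 16.1–16.2% | 8.0–8.2% | 7.7–7.8% | 3.8–3.9% |
| 0.6 | 15.4–15.6% | 7.7–7.8% | 7.4–7.5% | 3.7–3.8% |
| 0.8 | 13.9–14.0% | 7.0% | 6.7% | 3.4% |
| 0.9 | 12.5–12.6% | 6.2–6.3% | 6.0–6.1% | 3.0% |

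The reference for one two-sided 5% test is 5% in either direction and 2.5% in favour of resistance training. Every cell exceeds its reference.

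**Step 4. Where the excess comes from under a gate**

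At one visit, gated, the error is about 4.2%, so the gate deals with the two contrasts. What remains comes from repeating the procedure at a second visit.

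**Step 5. After a correction**

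- One named contrast at one visit: 5%.
- All four tests with Bonferroni at 0.05/4 = 0.0125: 3.4–4.7% over correlations 0.9 to 0.

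**The case against.** **The overall ANCOVA comes first.** The contrasts are introduced as a subsequent step, and testing contrasts only after a significant overall test is common practice. On that reading the error is about 7–8%, roughly half the ungated figure. This objection stands as far as it goes. The article does not say that the contrasts depend on the ANCOVA, so both readings are open and both figures must be given.

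**Not every false result would be reported as a benefit.** A reader might take 14–16.5% as the chance of falsely claiming that resistance training works. It is not: it also counts results in which resistance training looks worse than a comparator. The chance of a false favourable result is 7–8% ungated and 3–4% gated.

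**The contrasts answer different questions.** The Study design section adds Tai Chi to enrich the comparison, and the functional fitness section uses follow-up to see how long an effect lasts. Whether planned contrasts with distinct purposes need joint control is debated. These remarks hint at an order, but they do not set one.

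**A detail for the analysis plan.** A testing hierarchy is often left to that document. Here, however, the article itself fixes the tests, their level and where the correction goes. Followed as written, it leaves the randomised comparisons unadjusted.

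**More tests from the factor scores?** A reader might infer from the plural in "The primary outcomes (resilience scores" that the scale's factors ("equanimity, meaningfulness, ceaseless self-improvement, and self-reliance") will be tested too. The text does not support this. The outcome's own heading is singular, its cut-offs (126 and 145) apply to one overall score, and the factors are mentioned only as the scale's validated structure. The plural reads naturally as the participants' scores. All figures above count one score.

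**Conclusion.** The point holds: four between-group tests of the primary outcome, each at .05, none ranked and none adjusted. With no true difference between arms, the chance of at least one false significant result is about 14–16.5% if the contrasts do not depend on the ANCOVA and about 7–8% if they do, for an assumed between-visit correlation of 0.4 to 0.8. Over 0 to 0.9 the ungated range is about 12.5–17%. In favour of resistance training the figures are about 7–8% and 3–4%, against 2.5%.

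The documents do not support giving the larger figure as the trial's established error rate, because that depends on an unstated gating rule and an unstated correlation. No combination examined brings the error down to the nominal level. This should be corrected, but it does not call the design into question.

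**What to change.** State that the primary test is the Chinese Resilience Scale total score, resistance training versus control at post-test, at two-sided 5%. Then choose one of two treatments for the remaining contrasts:

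1. A fixed sequence written down in advance, each step at 5% and tested only if the step before is significant. For example: resistance training versus Tai Chi at post-test, then versus control at follow-up, then versus Tai Chi at follow-up. This holds the family-wise error for the four tests at 5%.
2. Label them secondary, and report estimates with confidence intervals.

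Say also whether the contrasts depend on the overall ANCOVA. Under either option the primary contrast should be tested directly, without that gate. All of this should be settled before results by group are seen.

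The change is wording only. It needs no extra participants, and the first test keeps the full 5%, which Bonferroni at 0.0125 would not allow. The price is that a later contrast cannot be claimed as confirmatory if an earlier step fails. In the example order, a failure against Tai Chi at post-test would close off both follow-up contrasts, so the order should reflect which claims matter most to the sponsor.
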